## Introduction

1

The prevalence of herpes labialis increases gradually in childhood, reaching 70% to 80% of adults worldwide.^[1–3]^ Recurrence of herpes occurs in 20% to 40% of the world's population.^[4]^ Herpes labialis are an infectious disease caused by the herpes simplex virus (HSV). HSV type 1 (HSV-1) and HSV-2 subtypes affect the skin and mucous membranes, but the HSV-1 subtype affects the orofacial region more. Recurrent herpes labialis can also be known as “fever blisters” or “cold sores.”^[5]^ Initial primary infections are usually more severe than recurrent ones, since the patient does not have acquired immunity.^[6]^ Herpetic gingivostomatitis usually occurs in young children characterized by painful oro-labial vesicles that coalesce and rupture forming ulcers, lasting between 10 and 14 days, accompanied by fever, malaise, fatigue, pain muscle, and dehydration.^[6–9]^

Clinically, the recurrence of the lesions goes through stages: prodromal, redness, papule, gallbladder, ulcer, crust, dry scaling, and remission of the lesion. Many of these stages may be short or imperceptible.^[6,10,11]^ It is a self-limiting, painful disease that generates discomfort, social restraint, and aesthetic compromise. In immunocompromised patients, recurrent lesions are more aggressive and take longer to heal.^[12,13]^ Because of these factors, associated with several recurrences, studies are important for other alternatives to treat herpes labialis, aiming to a fast resolution of the lesions, with less time of recurrence, without undesirable side effects.

Aciclovir is the most widely used medication to prevent or suppress HSV-1.^[10,14]^ Continuous use of these drugs may develop a high viral resistance.^[7,10]^ Antiviral medications are most effective when the patient is still in the prodromal phase. Aciclovir is effective in reducing the duration and symptoms of infection, but the optimal dose is still unknown.^[9]^ Although acyclovir decreases the duration of symptoms, it does not prevent recurrence.^[15–17]^ In view of the resistance that antiviral treatment can cause and the recurrence of the lesion, some alternative treatments have been studied, such as antimicrobial photodynamic therapy (PDT), which is a good option.^[18]^

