### Study variables and time

2.12

The primary study variable will be evaluation of the resolution time of the lesions in days (primary objective of the study). For this, a 15-day follow-up will be performed for this variable.

The secondary variables of the study will be

Follow-up of the recurrences of herpes simplex labialis (HSL) lesion at baseline (T0), 1 (T3), 6 months (T4), and 1 year (T5) follow-up periods.Presence of ballooning cells by exfoliative cytology at baseline (T0) and 3 (T1) days after injury.Evaluate if the amount of HSV-1 decreases after treatment with aPDT by Quantitative polymerase chain reaction q at the baseline (T0), 3 (T1), and 7 (T2).Evaluation of cytokines interleukin (IL)-6, IL-1β, IL-8, tumor necrosis factor alpha (TNF-α), and IL-10 by enzyme-linked immunosorbent assay method in nonstimulated saliva and HSL lesions in the baseline (T0), 3 (T1), 7 (T2), and 30 days after treatment (T3).To verify the presence of pain in HSL patients by HSL VAS at baseline (T0), 3 (T1), 7 (T2), and 30 days after treatment (T3).Check the temperature at the site of HSL lesion at baseline (T0), 3 (T1), 7 (T2), and 30 days after treatment (T3).Quality of life perception of HSL patients related to oral health will be assessed using the OHIP-14 questionnaire at baseline (T0) and 30 (T3) days after treatment.

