### Statistical analysis

2.14

Statistical analysis will be performed using only the data obtained from the patients who complete the study. The Kolmogorov–Smirnov test will be applied before the analysis of the normality of each parameter. The *t* test will be used to compare all means. All tests will be performed using Graphpad Prism 5 (Graphpad Software, San Diego, CA). Data will be presented on average and ±standard deviation. The level of significance will be set at *P* < .05.

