
This study will be a double-blind clinical trial with the goal of not inducing the researcher who will treat the patient to a positive aPDT result as well as to mask the participant's type of treatment. Blocked randomization was performed so that if there is any interruption of work for any reason, we will have groups with proportional numbers of participants, allowing comparison between them. After approval by the Research Ethics Committee of the Universidade Nove de Julho, patients will be invited to participate in the study by signing the ICF. If the lesions are in the vesicle stage, they will be topically anesthetized with 2% lidocaine gel, as directed by the Research Ethics Committee. Exfoliate cytology of the lesions will be performed as it is a simple and reliable method of confirming HSV infection, according to Barret et al. Microscopically we can observe changes in cytoplasm and nuclear structures. Lange et al,^[41]^ observed that cells exhibit a space between inclusion and the extended “bull's eye” cell membrane. In addition, he observed little frequency of ballooning cells, which are pathognomonic cells in herpes lesions.

Unstimulated saliva collection will be performed before treatment, 3, 7, and 30 days after the procedure, in both groups, to quantify the virus by qPCR and to evaluate the cytokines IL-6, IL-1β, IL-8, TNF-α, and IL-10. For HSV-1 amplification by qPCR, a set of HSVP1/HSVP2 primers will be used, which corresponds to DNA sequencing the eight human herpes virus described by Johnson et al. This primer amplifies HSV-1 subtypes, HSV-2, Epstein-Barr virus, and cytomegalovirus.^[32,33,42]^

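### The HSV-1 variable is worded as a fall after aPDT without naming the acyclovir comparison, and the single stated rule (t test, mean ± SD) on its plain reading analyses qPCR quantities on the raw scale

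*Protocol article*

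**What the plan says.** **Variable.** Section 2.12 lists the viral-load item among the secondary variables as "Evaluate if the amount of HSV-1 decreases after treatment with aPDT", by quantitative PCR at T0, T1 (day 3) and T2 (day 7). No comparator is named. The cytokine item in the same list is only an evaluation at four time points and carries no direction.

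**Analysis.** Section 2.14 covers every parameter with one rule. A Kolmogorov–Smirnov "test will be applied before the analysis of the normality of each parameter", the t "test will be used to compare all means", and "Data will be presented on average and ±standard deviation". It does not say whether the t test is paired or between arms, or what happens if normality is rejected. It mentions no transformation and no baseline adjustment. Only patients who complete the study are analysed.

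**Context.** The Introduction says of herpes labialis: "It is a self-limiting, painful disease that generates discomfort". The Discussion says that saliva is collected "in both groups, to quantify the virus by qPCR" and to measure cytokines. Section 2.1 sizes the trial at 12 per group on time to recovery, and section 2.5 adds three per group for dropout.

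**The concern.** There are two separate problems.

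1. **The contrast.** If the lesion resolves without treatment, viral load can be expected to fall in either arm as it heals. A statement that HSV-1 decreased after aPDT would then satisfy section 2.12 even if aPDT had no antiviral effect. The protocol presents aPDT as an alternative to acyclovir, so the informative question is aPDT against acyclovir.

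2. **The scale.** qPCR quantities typically spread multiplicatively. On raw copies, a few patients with high values can carry an arm's mean and inflate its SD. With about 12 completers per arm, a t test on raw means may then miss a large true difference.

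The viral-load result is the direct evidence on mechanism in this trial. It could be read as efficacy when it is natural healing, or a real difference could go unseen.

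**Working it through.** **The plan's own figures.** The 12 per group cannot be recomputed, because section 2.1 gives no hazard ratio, median or SD. The dropout step does reproduce: 24 / (1 − 0.20) = 30, or 15 per group. No SD or target difference is given for viral load or cytokines, so the spreads and effects below are assumptions, shown as a range.

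**Step 1: does a fall within the aPDT arm show an effect?** Assume no difference between arms, 12 patients, a natural fall of 1 log10 in both arms, and a baseline-to-follow-up correlation of 0.5. The SD of the paired difference is SD × √(2(1 − 0.5)) = SD. At SD 1.0 log10 the noncentrality is 1 / (1.0/√12) = 3.46 on 11 degrees of freedom (critical value 2.20). A paired log10 test is then significant in 88% of trials. At SD 1.5 the noncentrality is 2.31 and the figure is 56%. With a natural fall of 1.5 log10 or more it is about 100% at SD 1.0. A between-arm log10 test under the same conditions is significant in about 5%.

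On raw copies (simulated, baseline 6 log10, natural fall 1 to 3 log10), the same paired test is significant in about 83% to 88% of trials at SD 0.5, 15% to 30% at SD 1.0, and 3% to 9% at SD 1.5.

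**Step 2: power of the between-arm test, raw against log10.** True difference 1 log10, 12 per arm, two-sided 5% (sidedness is not stated). Log10 power comes from the noncentral t on 22 degrees of freedom (critical value 2.07), with noncentrality 1 / (SD × √(2/12)). Raw power comes from simulated log-normal data.

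| SD (log10) | Noncentrality | Raw power | Log10 power |
|---|---|---|---|
| 0.3 | 8.16 | 99.7% | 100% |
| 0.5 | 4.90 | 82% | 99.7% |
| 0.75 | 3.27 | 36% | 88% |
| 1.0 | 2.45 | 14% | 65% |
| 1.5 | 1.63 | 3% | 35% |

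With 15 per arm and SD 1.0, the figures are 18% and 75%. At 12 per arm, the largest patient supplies a median 52% of an arm's raw total at SD 1.0 and 69% at SD 1.5.

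**Step 3: baseline adjustment.** With the same assumed correlation of 0.5, adjusting log10 load for T0 raises power from 65% to 75% at SD 1.0, and from about 34% to 42% at SD 1.5 (simulated). Comparing raw change from baseline between arms has power of only 1% to 4% in every setting tried with a true 1 log10 difference.

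**Step 4: cytokines.** For a threefold difference at SD 0.43 log10 and 12 per arm, the noncentrality is 0.477 / (0.43 × 0.408) = 2.72. Log-scale power is about 74%, against 53% raw. The largest patient's median share is 26%. For a true halving, raw versus log power is 85% versus 90% at a natural-log SD of 0.5, 41% versus 53% at 0.8, 24% versus 37% at 1.0, and 15% versus 27% at 1.2.

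**The case against.** **The contrast is loose, not fixed as within-arm.** The trial is randomized and controlled, virus is quantified in both groups, and section 2.14 does not confine the t test to the aPDT arm. This stands. A reader might infer that the plan tests only the fall in the aPDT arm, and the document does not support that. What remains is that section 2.12 names no comparator and section 2.14 does not supply one.

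**The raw scale is inferred.** No section says untransformed copies, and a mean with SD could be reported for log10 values. A condensed article may also leave such detail to a fuller document. This stands in part. Raw scale is the plain reading, not an explicit statement. But section 2.14 does state a rule for all parameters and names no other scale, so the point is about a stated method and not only about silence.

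**A real difference need not be missed.** At SD 0.5 or below, raw power is 82% or more, and the document gives no SD. This stands. A reader might infer that a true arm difference would mostly go undetected. That holds only from roughly 0.75 log10 upward. At SD 1.5 even the log10 test has only about 35% power, so there the sample size is the larger limit: 80% power would need 2 × 1.5² × (1.96 + 0.84)² ≈ 36 per arm, against 16 at SD 1.0.

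**The two harms do not occur together on raw data.** Step 1 shows that spread large enough to hide an arm difference also largely hides the natural fall. This stands, so they should be treated as separate risks.

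**Cytokines are a weaker case.** This stands. Their item has no wording about a decrease after aPDT, no single patient dominates the mean, and the log-scale gain is modest.

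**Conclusion.** The point holds in limited form. The HSV-1 variable asks about a fall after aPDT without naming acyclovir, in a disease that the protocol itself calls self-limiting. A fall in that arm alone would not be evidence of an aPDT effect. The single analysis rule, read plainly, puts qPCR quantities on the raw scale and attaches no action to a failed normality test.

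The size depends on an SD that the document does not give. For a tenfold difference with 12 per arm, the raw scale costs almost nothing at SD 0.3, about 18 points at 0.5, and about 50 points at 0.75 to 1.0. At 1.5 it costs about 32 points, from a low starting level. For cytokines the cost is about 21 points for a threefold difference at SD 0.43 log10, and about 5 to 13 points for a halving. These figures assume log-normal data and a two-sided 5% test.

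This is a secondary variable and the primary outcome is not affected. It is a change worth making because it is nearly free.

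**What to change.** - **Section 2.12:** state the HSV-1 variable as the comparison of aPDT with acyclovir in HSV-1 quantity at T1 and T2. The Discussion also lists day 30 for viral quantification, so align the time points in the same edit.
- **Section 2.14:** analyse log10 HSV-1 quantity and log cytokine levels between arms, adjusted for the T0 value, and report ratios of geometric means with 95% confidence intervals. Describe within-arm change without presenting it as evidence of efficacy.
- **Undetectable values:** fix one convention before unblinding, since the log scale requires it.

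No new patients, samples or assays are needed. The downside is small: results read as ratios, and the convention for undetectable values has to be chosen. The change does not cure the small sample, so the intervals may be wide and a non-significant difference from acyclovir should not be read as equivalence.

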### Detailed study variables

2.13

#### Evaluation of injury resolution time in days

2.13.1

The patients will be followed up in 3 and 7 days and the resolution of the lesion will be monitored until it is completed. The completed will be accompanied by photos and telephone contact and noted in a specific clinical file. For this, a 15-day follow-up will be performed for this variable.^[15]^

#### Follow-up of HSL injury recurrences

2.13.2

Patients will be monitored at baseline (T0), 1 (T3), 6 (T4), and 1 (T5) follow-up periods. The complete will be accompanied by photos and telephone contact and noted in a specific clinical file. For this, a 1-year follow-up will be performed for this variable. The location of the lesions through sextants on the lips (sextants 1, 2, and 3 to upper left to right and sextants 4, 5, and 6 from right to left, with sextant 2 in the labial filter region and sextant 5 is its lower lip antagonist.

#### Presence of ballooning cells

2.13.3

Quantify the ballooning cells by means of exfoliative cytology.^[32]^

#### Collection of ballooning cells for exfoliative cytology

2.13.4

The swab on the lesion of the exfoliative cytology kit of the female swab specimen collection kit (Qiagen, Hilden, Germany) will be gently passed, made the smear on a slide for microscopic examination.

#### HSV-1 quantification

2.13.5

Collection of HSV lesions secretion: HSV lesion secretion samples will be collected at 1 single site in the central portion of the lesion with sterile swab after treatment of all HSV lesions. They will be stored in 500 μL of Tris-ethylenediaminetetraacetic acid in tubes of 1.5 mL for microcentrifuge (Eppendorf, Hamburg, Germany). During the collection period (in the clinic) the samples will be stored on ice inside a styrofoam. These samples will be properly identified and stored at −80°C (freezer from the UNINOVE Biophotonics Laboratory) until further analysis.

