### Treatment with photodynamic therapy

2.10

In group 2, patients will receive aPDT. The aPDT associates a photosensitive agent with a source of light and oxygen, to reduce the microbial load in places where there is no vesicle present.

The procedures will be performed as described:

1.If the lesions are in the vesicle phase, they will be ruptured with a sterile needle, and the overflow fluid will be cleaned with an absorbent paper taking care not to contaminate adjacent areas. The methylene blue solution at 0.005% concentration (Chimiolux; DMC, São Carlos, SP, Brazil) will be gently placed on the lesions.2.Application of methylene blue (0.05% Chimiolux 5 [DMC], purified water, and methylene blue) with a carpule syringe and needle (with stop and without bevel) on the lesions.3.One minute of preirradiation will be expected.^[29]^ The irradiations will be performed with the Laser Duo red laser diode (MMOptics, São Carlos, SP, Brazil) with a wavelength of 660 nm, with a power of 100 mW, energy density of 300 J/cm^2^, with energy of 3 J in the center of the lesion for 30 seconds.^[30]^ The laser head will be positioned in direct contact with the lesion perpendicular to the lesion.^[31]^4.It will be applied centrally to each isolated lesion that presents with fixed energy per point of 3 J.5.Wash in abundance with saline (saline solution) until the removal of the photosensitizer is complete.6.During the laser application both patient and operator will wear specific goggles to eye protection following the international security rules.7.Patients in group 2 will use placebo ointment as described in the following list.

The patients in group 1 (control-placebo of PDT) will receive an agent with the same vehicle as methylene blue to mimic irrigation with the photosensitizer and the laser will be switched off at the time of application.

The placebo PDT procedures will be performed on the lesion as described:

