1.Application of methylene blue placebo with a Carpule syringe and needle (with stop and without bevel) inside the lesions.2.One minute of preirradiation will be expected.^[29]^3.The irradiations will be performed with the same device positioned in the same way and at the same time of application; however, the laser will be turned off. The beep sound will be recorded and turned on during application to blind treatment to the patient.4.It will be applied exactly as described in group 2. It will be washed in abundance with saline (saline solution) until the total removal of the placebo from the photosensitizer.5.During the simulation of the laser application both patient and operator will wear goggles (Table 1).

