#### Salivary cytokine profile and HSV lesion secretion

2.13.8

The HSV lesion secretion samples will be collected with sterile swab at 1 site (central lesion site) and stored in 1.5 mL tubes for microcentrifuge (Eppendorf). The collected samples will be stored on ice. These samples will be properly identified and stored at −80°C (UNINOVE Biophotonics Laboratory) until further analysis.

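### The lesion swab for HSV-1 and cytokines is taken at one central site, which in the PDT arm is also the single irradiated point, so it may not represent the lesion and may distort the between-arm comparison of these secondary endpoints

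*Protocol article*

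**What the plan says.** Treatment (protocol article, section 2.10). The laser is used "with a power of 100 mW, energy density of 300 J/cm^2", "with energy of 3 J in the center of the lesion for 30 seconds". A later step adds: "It will be applied centrally to each isolated lesion that presents with fixed energy per point of 3 J". For the control arm, "The irradiations will be performed with the same device positioned in the same way and at the same time of application", but with the laser off. Control patients then spread acyclovir cream on the lesions themselves (section 2.11).

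Sampling. For viral quantification (section 2.13.5), "HSV lesion secretion samples will be collected at 1 single site in the central portion of the lesion with sterile swab". For cytokines (section 2.13.8), the lesion secretion samples "will be collected with sterile swab at 1 site (central lesion site"). No margin or whole-lesion swab is described for either assay.

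Endpoints (section 2.12). One secondary variable is to "Evaluate if the amount of HSV-1 decreases after treatment with aPDT by Quantitative polymerase chain reaction", at T0, day 3 and day 7. Another is cytokines in saliva and in the lesions at T0 and days 3, 7 and 30. HSV is also quantified in saliva (section 2, section 2.7 and the Discussion).

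Timing. Section 2.7 has the secretion and saliva samples taken first and treatment afterwards. The sentence on the swab in section 2.13.5 goes on to place collection after the lesions have been treated.

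**The concern.** Using the same swab site in both arms does not make the measurement neutral here. The light is delivered at one central point, so any gradient of effect from centre to margin in the PDT arm peaks where the swab is taken. The control arm has no such gradient: its laser is off and its active cream is spread over the lesions. Randomisation and blinding do not remove a difference that arises from where treatment and measurement coincide.

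If virus persists at the margin, a central swab would miss it, and the PDT arm could look better on lesion HSV-1 than the lesion as a whole would justify. The same applies to lesion cytokines. At stake is whether these mechanistic endpoints can be read as statements about the lesion. The Discussion cites a case series that irradiated four points around the lesion, so lesions extending beyond one point are within the authors' own view.

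**Working it through.** **Inputs from section 2.10:** power 100 mW, time 30 s, energy 3 J per point, energy density 300 J/cm², one central point per isolated lesion.

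**Step 1. Reproduce the stated energy.** Energy = power × time = 0.100 W × 30 s = 3.0 J. This agrees with the protocol.

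**Step 2. Implied spot.** Area = energy / energy density = 3 / 300 = 0.01 cm². Diameter = 2 × √(0.01/π) = 0.113 cm = 1.13 mm.

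**Step 3. Share of the lesion under the direct beam.** Lesion size is not given, so round lesions of diameter D are assumed. Share = (1.13/D)²: 14% at 3 mm, 5% at 5 mm, 2% at 8 mm, 1.3% at 10 mm.

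**Step 4. What a central swab could read.** Assumptions that are not in the documents: virus is evenly spread at the start, it falls by 2 log10 inside an effectively treated circle of diameter E, and it does not fall outside. For a region of diameter R (the swabbed area or the whole lesion), f = min(1, (E/R)²), and the measured fall is −log10[(1 − f) + f × 10⁻²]. Overstatement = fall in the swabbed area minus fall in the whole lesion.

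Worked example with E = 3 mm and a 5 mm lesion: f = 9/25 = 0.36, so the whole-lesion fall is −log10(0.64 + 0.0036) = 0.19. A swab inside the treated 3 mm reads 2.00. Overstatement = 2.00 − 0.19 = 1.81 log10.

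| Treated diameter E | Lesion | Swabbed diameter | Whole-lesion fall | Swab reading | Overstatement |
|---|---|---|---|---|---|
| 1.13 mm | 5 mm | 1.13 mm | 0.02 | 2.00 | 1.98 |
| 1.13 mm | 5 mm | 3 mm | 0.02 | 0.07 | 0.04 |
| 1.13 mm | 10 mm | 3 mm | 0.01 | 0.07 | 0.06 |
| 3 mm | 3 mm | any | 2.00 | 2.00 | 0 |
| 3 mm | 5 mm | 3 mm | 0.19 | 2.00 | 1.81 |
| 3 mm | 10 mm | 5 mm | 0.04 | 0.19 | 0.15 |
| 5 mm | 5 mm | any | 2.00 | 2.00 | 0 |
| 5 mm | 10 mm | 5 mm | 0.12 | 2.00 | 1.88 |

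(Falls in log10; differences taken before rounding.)

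The bias is nil when the treated area covers the lesion or the swab covers it. It is small when the swab is much wider than the treated area. It is large when the swab stays inside the treated area of a larger lesion. Light spread and a wide swab therefore do not simply add up as protections: light spread enlarges the zone within which a wide swab still sees only treated tissue.

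**Step 5. Direction.** The table assumes a T0 swab taken before irradiation, as in section 2.7. If T0 is swabbed after irradiation, as section 2.13.5 can be read, part of the central fall is already in the PDT arm's baseline. In the extreme case, with the full 2 log10 fall reached by T0 and held, the change from T0 at the swabbed point is 2.0 − 2.0 = 0, and clearance is understated.

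**The case against.** A reader might infer that the endpoint measures the irradiated spot instead of the lesion, and favours PDT by construction. The documents do not support that, for these reasons:

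- **Swabbed area.** The article speaks of a central portion and gives no area. With a 3 to 5 mm swab over a 1.13 mm treated spot, the illustration yields an overstatement of only 0.00 to 0.06 log10.
- **Lesion unit.** Each isolated lesion receives its own point. If these units are small, the shares for 5 and 10 mm lesions exaggerate the untreated part. Table 1, with the laser parameters, is not legible in the text available.
- **Persistence.** Follow-up swabs come at days 3 and 7 (and day 30 for cytokines). Nothing shows that a gradient from one 30-second exposure lasts that long.
- **Direction.** It depends on the unresolved timing of the T0 swab.
- **Saliva.** Virus and cytokines are also measured there, away from the laser point.
- **Endpoint wording.** The HSV-1 variable is worded as a decrease after aPDT. The comparison with acyclovir is inferred from the two-arm design and from the plan in section 2.14 to compare all means.

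All of this stands as a limit on the strength of the claim. None of it removes the coincidence of swab and beam. Saliva is a different matrix, and section 2 names virus at the injury site as a separate measure. Nor is the sampling site a detail left to a fuller document, since the article fixes it twice.

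A fixed central site is also a reproducible convention, and whole-lesion yield falls as the lesion shrinks. That would by itself favour an arm that heals faster. This is a real cost of the remedy and is dealt with under the fix.

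**Conclusion.** The point holds in a limited form. In the PDT arm only, the lesion swab is taken where the light dose is highest, so it may not represent the lesion and may distort the between-arm comparison of lesion HSV-1 and lesion cytokines. Under an assumed 2 log10 local fall and a pretreatment T0 swab, the overstatement of clearance lies anywhere between 0 and about 2 log10. The documents do not give the lesion size, swabbed area or light spread needed to narrow this, and the direction reverses if T0 is swabbed after irradiation. Only secondary endpoints are affected; the primary endpoint, resolution time in days, is not. The change should be made because it is cheap and removes a plausible one-arm distortion, not because a large bias has been shown.

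**What to change.** In sections 2.13.5 and 2.13.8, replace the single central site with one standardised swab pass over the whole lesion surface including the margin, identical in both arms and at each visit. Report HSV-1 relative to the total DNA that section 2.13.7 already quantifies by spectrophotometer, so that a shrinking lesion does not by itself lower the reading.

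Reconcile section 2.7 (samples before treatment) with section 2.13.5 (after treatment), so that the T0 swab is unambiguously a pretreatment baseline in both arms.

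Cost: protocol wording and a line in the examiner training of section 2.2. There is no extra sample or assay, and no treatment parameter changes. Downside: sample yield will depend on lesion area, and the total-DNA adjustment does not cover cytokines, so this limitation should be stated when lesion cytokines are reported.
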